## Abstract

**Background:**

Scapholunate advanced collapse (SLAC) and scaphoid non-union advanced collapse (SNAC) are common types of wrist osteoarthritis (OA). Non-operative treatment consists of pain medication, splinting, and avoiding activities that induce pain. However, in case a course of conservative treatment is unsuccessful, operative treatment is needed. The two most conventional operative approaches for SLAC/SNAC OA are four-corner arthrodesis (FCA) and proximal row carpectomy (PRC). Although FCA is the gold-standard operative technique and may lead to superior grip strength, the evident benefit of PRC is that it obviates any need for hardware removal and controlling for bony union. To date, no high-quality randomized controlled trial comparing FCA and PRC exists. As clinical outcomes seem comparable, a trial that assesses patient-reported outcomes, adverse events, and secondary operations may guide clinical decision making between these two procedures. Thus, the aim of this multi-institutional double-blind randomized controlled trial is to study whether PRC is non-inferior to FCA in treating SLAC/SNAC OA. We hypothesize that PRC is non-inferior to FCA with lower economic expanses.

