### EQ-5D-5L and cost-utility analysis

EQ-5D-5L is a standardized measure of health status developed by the EuroQol Group to provide a simple, generic measure of health for clinical and economic appraisal. Applicable to a wide range of health conditions and treatments, it provides a simple descriptive profile and a single index value for health status that can be used in the clinical and economic evaluation of health care. EQ-5D is designed for self-completion by respondents. It is cognitively undemanding and takes only a few minutes to complete [30]. In addition to health state evaluation, EQ-5D-5L will be used for the cost per quality-adjusted life year (QALY) gained evaluation after the procedure.

The costs will include treatment costs and possible costs of complications and sick leave. The costs of treatments and complications will be analyzed by collecting the actual use of healthcare services and multiplying the use of service by unit costs. Sick leaves and their societal costs will be collected from Social Insurance Institution of Finland (KELA).

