### Methods for additional analyses (e.g., subgroup analyses) {20b}

A cost-utility analysis (CUA) will be performed to compare financial aspects of FCA and PRC. The cost per quality-adjusted life year (QALY) method is used to compare the cost-utility ratio of FCA and PRC. The quality of health will be followed with EQ-5D-5L index and the change in this index at 1 year after surgery will be multiplied by the number of years spent in that health state to determine the number of QALYs gained or lost. To estimate QALYs gained or lost during patients’ lifetime, we will multiply the change in EQ-5D-5L index with the expected life years remaining. We will use the data from Official Statistics of Finland [32] to determine the life expectancy for each patient. We will use a constant discount rate of 5% when calculating the total QALYs gained over lifetime to account for a projected diminishing gain over time [33]. To calculate cost of QALY, we will divide the total expenses of FCA and PRC with the change of EQ-5D-5L. This will be adjusted to give the cost per QALY over the course of lifetime.

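### The cost-utility analysis compares each procedure's average cost per unit of EQ-5D-5L change instead of incremental cost with incremental QALYs, and can rank the procedures wrongly when the costlier one also gains more

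*Protocol article*

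**What the plan says.** Section {20b} of the protocol article sets the purpose: "A cost-utility analysis (CUA) will be performed to compare financial aspects of FCA and PRC". The decision statistic follows: "The cost per quality-adjusted life year (QALY) method is used to compare the cost-utility ratio of FCA and PRC". The formula is then given: "To calculate cost of QALY, we will divide the total expenses of FCA and PRC with the change of EQ-5D-5L".

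The same section takes the change as the movement in the EQ-5D-5L index at 1 year after surgery. For the lifetime version, "we will multiply the change in EQ-5D-5L index with the expected life years remaining", and "We will use a constant discount rate of 5% when calculating the total QALYs gained over lifetime". The ratio is carried over to that horizon: "This will be adjusted to give the cost per QALY over the course of lifetime".

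The section on EQ-5D-5L and cost-utility analysis describes the numerator: "The costs will include treatment costs and possible costs of complications and sick leave". The abstract states the economic expectation as a comparison between the procedures: "We hypothesize that PRC is non-inferior to FCA with lower economic expanses".

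The article nowhere mentions an incremental cost, an incremental QALY, an ICER, a net benefit or a willingness-to-pay threshold.

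**The concern.** The trial asks an economic question about two active procedures: if one costs more, what does the extra money buy? That needs the between-arm difference in cost set against the between-arm difference in QALYs. The stated formula gives instead, for each procedure, the average cost per unit of improvement over the patients' own baseline.

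This has three consequences.

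- An average ratio uses doing nothing, with no change from baseline, as its implicit comparator. The trial has no such arm, and it is not the choice being made.
- The before-after change includes natural course and regression to the mean. Randomisation makes these similar in the two arms, so they cancel in a difference. They do not cancel in a ratio.
- A ratio with a small denominator is unstable, and it has no useful meaning when the denominator is negative.

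At stake is the ranking of the two procedures on cost-utility, which readers would take as the trial's economic conclusion.

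**Working it through.** The protocol gives no costs, utility gains or threshold, so there is no figure of its own to reproduce. From the protocol come the form of the ratio, the 5% discount rate and the multiplication by remaining life years. Everything else below is assumed, and the currency unit is arbitrary.

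**Formulas.** C is mean cost and g is mean gain in index. A = (1 − 1.05^−T)/0.05 is the discounted number of years over T years.

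- Plan's rule: compare C/g between arms, or C/(g × A) over a lifetime.
- Incremental rule: ICER = (C_FCA − C_PRC) / [(g_FCA − g_PRC) × A]. If FCA costs more and gains more, it is preferred when the threshold exceeds the ICER.

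**Example 1.** PRC 6,000 with gain 0.20; FCA 8,000 with gain 0.25.

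- Plan's ratios: 6,000/0.20 = 30,000 and 8,000/0.25 = 32,000. PRC looks better.
- Lifetime, T = 25: A = 14.09. The ratios become 30,000/14.09 = 2,129 and 32,000/14.09 ≈ 2,270. The ranking is the same, because randomised arms should have similar life expectancy and both denominators are scaled by about the same factor.
- Incremental, one year: 2,000/0.05 = 40,000 per QALY.
- Incremental, 25 years: 0.05 × 14.09 = 0.70 QALY, and 40,000/14.09 ≈ 2,840 per QALY.
- Range over T: A = 7.72 at 10 years gives about 5,180 per QALY; A = 17.16 at 40 years gives about 2,330.

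On the 25-year horizon any threshold above about 2,840 prefers FCA, although the average ratios point to PRC. On one year, thresholds below 40,000 prefer PRC under both rules.

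**Example 2, opposite direction.** FCA 8,000 with gain 0.20; PRC 5,000 with gain 0.10; one year.

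- Plan's ratios: 40,000 (FCA) and 50,000 (PRC). FCA looks better.
- ICER: 3,000/0.10 = 30,000. At an assumed threshold of 20,000 the net benefit of FCA is 20,000 × 0.10 − 3,000 = −1,000, so PRC is preferred.

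**Where the rules agree.** Costs FCA 8,000 and PRC 5,000, T = 25, threshold 20,000.

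| Gain FCA / PRC | Average ratio FCA / PRC | Net benefit of FCA over PRC | Both favour |
|---|---|---|---|
| 0.15 / 0.15 | 3,784 / 2,365 | −3,000 | PRC |
| 0.15 / 0.20 | 3,784 / 1,774 | −17,094 | PRC |
| 0.20 / 0.19 | 2,838 / 1,867 | −181 | PRC |

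**Effect of a component common to both arms.** In example 1, suppose 0.10 of each gain is natural course and regression to the mean. Removing it leaves gains of 0.10 and 0.15, and the between-arm difference is still 0.05. The average ratios become 6,000/0.10 = 60,000 and 8,000/0.15 ≈ 53,333, which now favour FCA. The ICER is unchanged. The plan's ranking therefore depends on something that has no bearing on the choice between the procedures.

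**Instability.** 8,000/0.02 = 400,000; 8,000/(−0.01) = −800,000.

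**The case against.** The strongest reply is that this is an additional analysis and that its consequences are easily overstated. Much of that is right.

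- A reader might infer that the randomised comparison is lost. It is not. EQ-5D-5L is a listed secondary outcome, and section {20a} compares continuous outcomes between the randomised groups with baseline as a covariate and intention-to-treat as primary. Costs can also be tabulated by arm. What is missing is a measure that combines the two differences.
- A reader might treat the economic claim as half of what the trial tests. The sample-size section {14} confines the primary hypothesis to PRWE, Table 1 lists no cost endpoint, and lower expenses alone could be shown by a cost difference.
- A reader might assume that PRC is expected to be cheaper but slightly worse in utility. The protocol says no such thing. Its introduction reports generally similar patient-rated outcomes and cites a meta-analysis that found PRC statistically better on motion, grip and pain. If PRC is cheaper and at least as good, both rules give the same answer.
- A reader might see a contradiction between lifetime QALYs and short-term costs. The cost section names cost types but gives no time limit, so a mismatch is only an inference.

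It is also true that reading the formula as one ratio per arm is an interpretation. The stated aim of comparing the ratios of the two procedures makes it much the most natural one. Finally, a condensed article may leave economic detail to a fuller document. That defence does not reach this point: the formula is stated, and what is stated is not an incremental comparison.

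**Conclusion.** The point holds in a limited form. The protocol fixes an average-ratio comparison that does not answer the between-arm economic question, and the lifetime rescaling does not repair it. The ratio can rank the procedures wrongly in either direction when the costlier procedure also gains more QALYs. Whether it does so depends on costs, gains, horizon and threshold, none of which the protocol gives. The illustration (30,000 against 32,000 favouring PRC, with a 25-year incremental cost of about 2,840 per QALY for FCA) assumes that a 0.05 gap in the index persists unchanged for 25 years. It shows that a reversal is possible, not that one is likely.

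It would go too far to say that the analysis will misrank the procedures. If one proves cheaper and at least as effective, the ranking is the same under both rules. The PRWE non-inferiority analysis and the sample size do not depend on any of this. The change should be made, but it concerns an additional analysis.

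**What to change.** In section {20b}, replace the ratio formula with an incremental comparison as the main result of the cost-utility analysis:

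- the intention-to-treat difference between PRC and FCA in mean cost;
- the intention-to-treat difference in mean QALYs, adjusted for baseline EQ-5D-5L index;
- the two reported jointly, as incremental net benefit or an ICER, with the uncertainty of the joint result. If net benefit is used, the threshold or range of thresholds should be fixed before unblinded results are seen.

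Use the within-trial period as the base case for both costs and QALYs; the 12 months to which the stated EQ-5D-5L change refers is the natural choice. Keep the lifetime extrapolation as a secondary scenario, with its assumption about how long the between-arm difference lasts stated openly. The interval method can be left to the analysis plan.

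The cost is a reworded paragraph and a modest amount of analysis. The base case needs no new outcome measure, because EQ-5D-5L, service use and sick leave are already to be collected. Only the lifetime scenario could need more: cost projections beyond follow-up, if its costs are to cover the same horizon as its QALYs.

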Although several studies report the outcomes of PRC and FCA, there is a paucity of high-quality evidence that would support the use of one technique over another. Two RCTs exist comparing these techniques [6, 7]. However, these trials suffer from methodological shortcomings, such as lack of blinding, high risk of selection bias, and incomplete outcome reporting. Generally, studies show no significant difference in ROM, grip strength, pain, or patient-rated outcomes [6–8]. However, some study groups suggest that FCA may be superior in terms of grip strength, while PRC may be preferable in terms of ROM, postoperative complications, and secondary operations [9–12]. Some studies indicate that PRC is more cost-effective [13, 14], while Daar et al. [15] concluded that FCA with cannulated compression screws is the most cost-effective approach. A long-term study reported fewer arthritic changes after FCA versus PRC. However, there was no apparent correlation between radiographic OA and patient satisfaction [16].

The most recent meta-analysis comparing PRC and FCA from Kamir et al. (2020) used flexion/extension ROM, grip strength, and pain level as outcome measures. They found that PRC was statistically but not clinically significantly better than FCA in all outcome measures [17].

Wrist OA due SLAC- and SNAC-degenerative pattern remains a common disorder encountered by a wrist surgeon. To date, most surgeons will choose to manage patients with SLAC/SNAC OA with FCA over PRC. However, the use of PRC has gained popularity among clinicians due its simplicity and predictable results, without the need to remove hardware or control for bony union. We hypothesize that PRC is non-inferior to FCA with lower economic expanses. While superiority of either procedure may be insurmountable to present, a thorough assessment of important considerations, such as AEs, postoperative pain, ROM, and convalescence time, should be examined by means of a randomized controlled trial (RCT). Thus, we planned a study protocol for a multicenter, double-blinded, randomized controlled non-inferiority trial comparing PRC vs FCA for the treatment of SLAC/SNAC I-II OA of the wrist.

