Although a growing number of scientific papers have been published comparing these different techniques for FCA, no RCTs have been conducted. Based on non-randomized comparisons, the outcomes seem comparable [10, 15, 38, 39] and long-term outcomes of FCAs are reasonable [12, 40–42]. In this trial, we chose cannulated compression screws for rigid internal fixation to allow early ROM exercises and to ensure concealment of treatment allocation (no implant removal). All four “corners” will be decorticated and fused to achieve generalizable results. Cancellous bone graft is used to enhance ossifying potential [43, 44]. However, the placement, number, diameter, and length of the screws will be left to the surgeons’ discretion without compromising stability of the fixation.

PRC was described in 1944 by Stamm [45] and has regained popularity among surgeons treating wrist OA. The rationale for this procedure is similar to FCA, namely to preserve as much motion as possible while treating pain by relocating contact and motion of the wrist to a healthy articular cartilage. PRC is a rather easy procedure to perform and avoids the risk of bony non-union, implant loosening, breakage, and removal. The long-term outcomes of PRC have previously been shown to be rather good when compared to FCA long-term outcomes [16, 44, 46]. The possible disadvantages are mainly due shortened bony frame, which is hypothesized to cause impaired grip strength and impingement between the trapezium and radial styloid. Moreover, unlike FCA, PRC may not be performed on patients with advanced OA present at the head of the capitate, such in SLAC/SNAC III [19]. In this trial, patients with marked OA of the capitate head will be excluded. As with FCA, a pragmatic approach will be used for PRC, allowing the surgeon to perform radial styloidectomy when deemed necessary.

The pragmatic execution of the procedures will allow the surgeon to treat the patient according to the unique clinical presentation of the condition. However, this might also be interpreted as a limitation, as variation in the technique may potentially affect outcomes. However, we are not aware of any evidence that the modifications would affect the results and the pragmatic setting improves generalization. Another limitation is that the staff in the operation room cannot be blinded to the allocation. This is unlikely to cause performance bias as the surgeon and other operating room staff are excluded from postoperative treatment.

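### The cost-utility ratio sets lifetime QALYs against costs that cover only the observed period, with no stated cost window and no projection of later costs

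*Protocol article*

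**What the plan says.** The benefit side is in the protocol article's section on additional analyses {20b}. The EQ-5D-5L input is measured once: "the change in this index at 1 year after surgery will be multiplied by the number of years spent in that health state". It is then extended to life expectancy: "To estimate QALYs gained or lost during patients’ lifetime, we will multiply the change in EQ-5D-5L index with the expected life years remaining". Discounting is stated for this side only: "We will use a constant discount rate of 5% when calculating the total QALYs gained over lifetime". The ratio follows: "To calculate cost of QALY, we will divide the total expenses of FCA and PRC with the change of EQ-5D-5L". The next sentence turns it into a lifetime figure: "This will be adjusted to give the cost per QALY over the course of lifetime". How that adjustment is made is not described.

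The cost side is in the section on EQ-5D-5L and cost-utility analysis. Costs comprise treatment, complications and sick leave. Treatment and complication costs "will be analyzed by collecting the actual use of healthcare services and multiplying the use of service by unit costs", and sick leave is taken from the national social insurance register. Neither section gives a period over which costs are counted.

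Follow-up visits end at 10 years (Outcomes {12}; Participant timeline). A complication leading to re-operation is a recorded major adverse event (Adverse events).

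**The concern.** Actual use of services exists only for the time over which it is observed, whereas the QALYs are credited for the rest of life. The two sides of the ratio therefore cover different periods. A cost that arises after observation stops is not merely left undiscounted; it does not enter at all. The ratio is too low by whatever those costs would have been.

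The omission need not be equal in the two arms. The Background mentions studies suggesting that PRC may be preferable for secondary operations. It also states: "A long-term study reported fewer arthritic changes after FCA versus PRC". The Discussion says that PRC "avoids the risk of bony non-union, implant loosening, breakage, and removal".

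Economics is part of what the trial sets out to show. Lower cost with PRC belongs to the stated hypothesis, and a cost-effectiveness analysis is named under Objectives {7}. A headline lifetime cost per QALY built on unmatched periods would be a weak answer to that question.

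**Working it through.** The protocol gives no cost, QALY or cost-per-QALY figure, so there is nothing of its own to reproduce. The sums below illustrate how large the mismatch can be.

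**Inputs from the protocol.** Discount rate 5%; QALY horizon equal to remaining life expectancy; last follow-up at 10 years; entry age 18 to 75 years (Table 2), so remaining life varies widely.

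**Assumptions.** Remaining life L of 10 to 50 years; cost window W of 1 year (the time point of the EQ-5D-5L input) or 10 years (the longest follow-up); late re-operation rates and prices as stated in each step.

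**Step 1. Discounted life-years.** A(L) = (1 − 1.05^−L) / 0.05. This gives A(1) = 0.952, A(10) = 7.72, A(20) = 12.46, A(30) = 15.37, A(32) = 15.80, A(40) = 17.16, A(50) = 18.26.

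**Step 2. Share of credited QALYs that fall after costs stop.** Share = 1 − A(W)/A(L). The yearly gain is carried forward unchanged, so it cancels and the share does not depend on its size.

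| Remaining years L | W = 1 year | W = 10 years |
|---|---|---|
| 10 | 88% | 0% |
| 20 | 92% | 38% |
| 30 | 94% | 50% |
| 40 | 94% | 55% |
| 50 | 95% | 58% |

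For example, at L = 20 and W = 10: 1 − 7.72/12.46 = 0.38.

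**Step 3. Present cost left out per point of late re-operation risk.** Assume that a late re-operation costs as much as the index operation and that the risk is 1 percentage point per year to the end of L.

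- L = 32, costs counted for 1 year: 0.01 × (15.80 − 0.952) = 0.149 of an index operation.
- L = 32, costs counted for 10 years: 0.01 × (15.80 − 7.72) = 0.081.
- L = 20, costs counted for 1 year: 0.01 × (12.46 − 0.952) = 0.115.
- L = 40, costs counted for 1 year: 0.01 × (17.16 − 0.952) = 0.162.

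This is a demanding scenario: at L = 32, 1 point per year over the 31 years after the first is about 31 re-operations per 100 patients. The protocol gives no rate to support or refute it.

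**Step 4. Effect on one arm's ratio.** If the omitted late cost is a fraction f of the observed cost, the ratio is too low by f/(1 + f).

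- Late risk 5% at half the observed cost per patient: f = 0.05 × 0.5 = 0.025, so about 2%.
- Late risk 20% at the full observed cost: f = 0.20, so 0.20/1.20, about 17%.
- The same extremes discounted at 5%: f = 0.025/1.05^15 = 0.012 gives about 1%, and f = 0.20/1.05^3 = 0.173 gives about 15%.

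**The case against.** **Detail held elsewhere.** A journal article condenses the full plan, and a cost window or cost discounting rule may sit in a health-economic document that is not shown. That is fair, and the missing detail alone would not be a finding. What remains is the asymmetry in the rules that are stated: QALYs are projected to life expectancy and discounted, while costs are described as actual use only. The undefined adjustment to a lifetime figure might include a cost projection, but nothing in either section says so.

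**All late operations priced at zero.** A reader might infer that every late re-operation or hardware removal is left out, or that costs stop at 1 year. The documents do not support this. Complication costs are included, no 1-year limit is given, and follow-up to 10 years could capture late operations if costs are counted that long. With a 10-year window and 10 remaining years there is no mismatch. Only costs after the observed period are lost.

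**A known direction of bias.** A reader might also infer that one arm is systematically favoured. The protocol does not allow that conclusion. Its compression screws were chosen partly so that implants need not be removed. CBCT runs to 12 months, so some non-union costs may fall inside even a short window. The remark on arthritis after PRC is followed by a statement that radiographic change showed no apparent correlation with satisfaction, and no cost is attached to it. If FCA does have more late operations, omitting them favours FCA and makes a claim of lower cost with PRC conservative.

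**Mis-ranking.** The figure of 0.149 does not mean that any cost gap below about 15% of the index operation puts the arms in the wrong order. A cost ranking can reverse only if the arm that is cheaper within the window also has the higher late risk. Ranking on cost per QALY depends on the QALYs as well. The hypothesis of lower cost is about costs, so the long QALY horizon cannot decide it; the cost window can.

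**Conclusion.** The point holds in a limited form. As written, a lifetime QALY denominator meets a cost numerator that covers at most the observed period, and this is so even if costs are counted for the full 10 years, except for patients with about 10 remaining years or fewer. Cost per QALY is understated to the extent that late costs occur.

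The extent cannot be fixed from the protocol, which gives no unit costs, late re-operation rates, life expectancies or cost window. The period mismatch in Step 2 rests only on the 5% rate and the assumed L and W. The effect on an arm's ratio, roughly 1% to 17%, rests on assumed late risks of 5% to 20% priced at 0.5 to 1.0 times the observed cost per patient. Whether the two arms are affected differently, and which way, is open.

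The cost-utility analysis is an additional analysis. The primary comparison of PRWE at 1 year is not touched.

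**What to change.** In the section on EQ-5D-5L and cost-utility analysis, state the period over which service use and sick leave are counted. In the section on additional analyses {20b}:

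- Make the base case a matched horizon, with costs and QALYs both to 12 months.
- Repeat it with both to 5 and to 10 years if EQ-5D-5L and service-use data are collected at those visits. The schedule table is not visible in the text at hand, so this needs checking.
- Report the lifetime figure only as a scenario in which late costs are projected in both arms and discounted at the same rate as the QALYs, with sensitivity analysis on the late re-operation rates.
- Say what the lifetime adjustment of the ratio consists of.

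A 12-month base case does not capture late operations either. Its merit is that both sides cover the same period; the longer repeats and the scenario carry the information on late costs.

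The price is a change of wording and a little modelling, more if 5- and 10-year service use is not already collected. The headline cost per QALY will look less favourable.
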